## Abstract

**Introduction:**

This paper outlines the study protocol for the Dutch Young People (YP) Face IT Study. Adolescents with a visible difference (ie, disfigurement) often experience challenging social situations such as being stared at, receiving unwanted questions or being teased. As a consequence, some of these adolescents experience adverse psychosocial outcomes and appearance-related distress. To address this appearance-related distress, an online psychotherapeutic intervention, YP Face IT, has been developed. YP Face IT uses social interaction skills training and cognitive–behavioural therapy. The Dutch YP Face IT Study tests whether this intervention is effective in reducing social anxiety and improving body esteem.

**Methods and analysis:**

Participants are adolescents aged 12–18 with a visible difference and experiencing appearance-related distress. In this two-armed randomised controlled trial, 224 adolescents will be randomised to care as usual or YP Face IT. Adolescents will complete questionnaires at baseline, at 13 weeks and at 25 weeks. Primary outcomes are differences in social anxiety and body esteem between YP Face IT and care as usual. Secondary outcomes are differences in aspects of self-worth, perceived stigmatisation, health-related quality of life, life engagement, appearance-related distress and depressive symptoms between the two groups.

**Ethics and dissemination:**

Research ethics approval was obtained from the medical ethics review committee in Rotterdam (reference number MEC-2018-052/NL63955.078.18). Findings will be disseminated through academic peer-reviewed publications, conferences and newsletters to patient associations and participants of the study.

**Trial registration number:**

The Netherlands Trial Register (NL7626).

Strengths and limitations of this studyThis is the first randomised controlled trial to assess Young People Face IT, an online psychosocial intervention for adolescents with a visible difference.Measurements include a direct follow-up and follow-up 3 months after completion of the intervention.Participants are recruited throughout the Netherlands, enhancing generalisability.Participants are not blinded to allocation, which could lead to reporting bias.

## Introduction

Having a visible difference can have a substantial impact on one’s life. People with a visible difference commonly encounter difficult social situations, such as being stared at, receiving unwanted questions and feeling isolated. A visible difference (ie, disfigurement) to the face or body occurs in 1 in 44 people, a visible difference solely to the facial area in 1 in 111.^1^ A visible difference can be either congenital (eg, cleft lip and palate and craniofacial conditions), result from a skin condition (eg, vitiligo, psoriasis and acne), trauma (eg, burns and scars), disease (eg, cancer, meningitis and alopecia areata) or medical treatment (eg, surgery or radiotherapy). Whether someone identifies as having a visible difference is a subjective experience. A clear definition of what a visible difference is can thus not be given.

Some studies show that adolescents with a visible difference experience no additional psychosocial problems^2 3^ and even perceive their friendship, social acceptance, appearance and emotional distress in a more positive way than unaffected peers.^4^ However, reviews show that a significant number of adolescents with a visible difference do experience adverse psychosocial outcomes.^5–7^ More specifically, they experience higher levels of minor psychological disturbance, self-consciousness in public situations, neuroticism,^8^ internalising symptoms^7 9^ and anxiety, depression and difficulties with social functioning.^10^ Furthermore, parents perceive their children as being more shy and inhibited.^11^

Available interventions for adolescents or adults with a visible difference are scarce and lack evidence base.^12–15^ Research often lacks a solid design and overall methodological quality and yields small effect sizes. However, there is some support for models involving social skills training (SST), cognitive–behavioural therapy (CBT)^12 14 15^ and self-help for managing anxiety.^13^

Young People (YP) Face IT was developed in the UK, in collaboration with adolescents and the charity Changing Faces.^16^ YP Face IT was derived from the adult intervention Face IT, which was found to be effective at reducing anxiety, depression and appearance concerns while increasing positive adjustment.^17^ In an acceptability and feasibility study concerning YP Face IT, the intervention was found to be acceptable, with most of the adolescents thinking it would help them improve their confidence and self-acceptance and help them develop new skills in dealing with difficult social situations.^16^

### Aims

In sum, interventions aimed at adolescents with a visible difference are scarce and have limited evidence to support them. The available evidence, however, does point to SST and CBT as being potentially effective methods for managing psychosocial difficulties among people with a visible difference. In an attempt to provide adolescents coping with a visible difference with an effective intervention focussing on improving emotional resilience, the Dutch YP Face IT Study aims to test an online psychotherapeutic intervention combining social interaction skills training (SIST) and CBT. More specifically, the aims of the current study are to test the effectiveness of the Dutch version of YP Face IT in reducing anxiety and improving body-esteem among Dutch adolescents with a visible difference.

## Methods and analysis

To assess the effectiveness of the Dutch version of YP Face IT, a randomised controlled trial (RCT) will be conducted.

### Participants

This study will be conducted in a Dutch academic hospital. The target group for this study is Dutch adolescents aged 12–18 with a visible difference and experiencing appearance-related distress. Recruitment will take place throughout the Netherlands.

Adolescents will be eligible for participation if they are aged between 12 and 18, have a visible difference and access to a computer with internet and experience appearance-related distress. The appearance-related distress is operationalised as an elevated score on either social anxiety or depression or a lower score on body esteem, as assessed by self-reports.

Exclusion criteria are a mental disability, reading ability below 12 years of age, visual impairments preventing comprehension of the online intervention, a clinical diagnosis of depression, psychosis, body dysmorphic disorder or an eating disorder and insufficient proficiency of Dutch. Furthermore, adolescents who receive face-to-face care by a psychologist will be excluded from participation.

### Intervention

YP Face IT (Dutch: *Face IT voor jongeren*) is an online psychotherapeutic intervention^16^ specifically designed for adolescents and developed in cooperation with adolescents and the British charity Changing Faces. The intervention is aimed at helping adolescents cope with some key concerns people with a visible difference may have, such as anxiety, depression, low self-esteem and appearance-related distress.

YP Face IT combines SIST with CBT. The intervention consists of 7 weekly sessions and an additional booster session after 6 weeks, helping the adolescent recall what was learnt during the weekly sessions. The first three sessions focus on SIST, sessions 4–6 focus on CBT and session seven is a summary of all learnt techniques. Session eight is a booster quiz, 6 weeks after session seven. The content of each session is displayed in table 1. Each session has different exercises and activities and takes 45–60 min to complete. In addition to the weekly sessions, participants will also be asked to complete small homework assignments between sessions. Participants will have access to an online journal in which they can write about their experiences and enter the answers to the homework assignments. Participants will have the opportunity to contact the research team if they are struggling with the homework activities. A reminder email is send if the participant has not entered data relating to the homework activity in their journal within 5 days following their last session.

**Table 1 T1:** Content of the YP Face IT intervention

Session	Content	Type	Week
1. Common problems	Common problems experienced by adolescents with a visible difference: bystander responses, teasing, bullying.	SIST	1
2. Improve your social skills	Body language, verbal and non-verbal skills and building positive social skills.	SIST	2
3. Don’t be SCARED, REACH OUT	Effect of own behaviour on other people. Toolbox of techniques to cope with difficult social situations.	SIST	3
4. Think, Feel, Do	Relationship between thoughts, feelings and behaviours. Identifying negative thoughts and using a positive voice to challenge these thoughts. Different coping strategies for negative thoughts.	CBT	4
5. SMART goals	Using SMART goals to help achieve goals, dividing the end goal into subgoals. Dealing with concerns in romantic relationships.	CBT	5
6. Beating anxiety	Exposure therapy in the form of a fear ladder. Relaxation techniques.	CBT	6
7. Looking at your progress	Summary session, with summary of all previous sessions.	SIST/CBT	7
8. Booster quiz	Quiz with 16 questions on all taught techniques.	SIST/CBT	13

CBT, cognitive–behavioural therapy; SIST, social interaction skills training; YP, Young People.

YP Face IT is designed as a self-help intervention, without any active guidance by a psychologist. Adolescents work through the sessions on their own. Parents receive a short description of each session and will receive the reminders, but are not involved in the sessions themselves.

Monitoring will take place to assess whether adolescents complete the homework assignments and whether they are struggling in any way with the intervention or their mental health. Monitoring will be done by an experienced clinical psychologist and a master’s student. Should we find that adolescents experience severe psychological symptoms, they are referred to other care that may better suit their needs.

#### Care as usual (CAU)

CAU will consist of regular medical care. The type of the care may differ depending on the condition (eg, skin care for eczema and orthodontics for cleft palate). Psychological care is not part of CAU. However, medical personnel will monitor the adolescents’ well-being as part of CAU. They may refer the adolescents to a psychologist in case of suspicions of psychological problems. Adolescents that receive psychological care during participation in the study will not be allowed further participation.

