### Recruitment

Participants are recruited through several channels. The first is through patient organisations. Patient organisations will be approached and asked if they are willing to advertise the Dutch YP Face IT Study on their website and in their newsletters. If an adolescent is willing to participate, he/she is encouraged to send an email to the research team, providing his/her contact details. The adolescent will then receive an information package containing a patient information letter, an informed consent form and a response card. The second channel is through our website (www.faceitvoorjongeren.nl). On our website, adolescents can read information about YP Face IT and contact the research team. If they do so, they will receive an information package. The third channel is through the Erasmus MC-Sophia Children’s Hospital. Subjects will be drawn from the department of child and adolescent psychiatry/psychology, the department of plastic and reconstructive surgery, the department of oral and maxillofacial surgery and special dental care and the department of dermatology. Subjects will be informed about the study by their treating doctor/clinician. It will be explicitly stated that participation is voluntary and that they can withdraw from the study at any time should they wish to do so. After informing the potential participant, they will receive an information package. If a potential participant does not have regular appointments at the Erasmus MC-Sophia Children’s Hospital, we will send an information package to their home address.

A response card will be included in the information package. On this response card, adolescents can indicate whether they give permission to be contacted by the research team. If the response card has not been returned within 2 weeks, the research team will contact the adolescent.

If participants are willing to participate, they are asked to fill in a consent form. For participants younger than 16 years, both parents are required to sign the informed consent form. After receiving the informed consent form, the researchers will include the participant in the trial and send out the first set of online questionnaires.

Participants will receive a gift card worth €10, after completing the entire study. If a participant decides to withdraw from the study prematurely, the adolescent will not receive a gift card.

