### Randomisation and blinding

Participants will be randomised to either the CAU or the YP Face IT group in a 1:1 ratio. Randomisation will be stratified by age (12–13, 14–15 or 16–17 years old). Randomisation will be done using a list with a random sequence, generated using a computer programme. With the stratification, six different types of blocks can be formed. Each block will independently vary between four and eight randomisation pairs. The adolescents are informed of the group they are randomised to through email. The researcher analysing the data will be blind to the randomisation and will not be involved in monitoring the adolescents in the intervention. This researcher also supervises data collection by students, who are not blinded. The participants, the clinical psychologist and students monitoring the adolescents in the intervention will not be blind to the treatment conditions. When contacting the research team, the adolescents are explicitly instructed not to talk about the group they were allocated to.

If, through monitoring, the research team suspects that a participant experiences clinically significant symptoms, unblinding may take place. The participant will be excluded from the study and will be transferred to more appropriate care.

Participants that drop out after randomisation will be asked if they are willing to complete the questionnaires at T2 and T3. They are in no way obliged to do so.

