### Statistical analysis

The data will be analysed using multilevel linear regression analyses. There will be two levels in the models. The participants constitute the upper level and their repeated measures the lower level. For each outcome variable, a model will be postulated using treatment group, time and interaction with treatment group as fixed effects. Time will be entered in two ways: categorical and continuous. First, for categorical, we will postulate a model with T2 (direct follow-up) and T3 (3-month follow-up) using T1 (baseline) as reference group. Second, for continuous, we will apply the logarithm of time, as generally treatments have the largest effect at start and the level of functioning stabilises on the long run. The deviance statistic using restricted maximum likelihood will be applied to determine the covariance structure. The deviance test will be used to determine whether the more parsimonious (log) model is a too rigorous oversimplification.^35^ Effect sizes will be calculated from dividing differences between the primary time point (ie, 3 months) estimations and baseline by the estimated baseline SD. Analyses are done on an intention-to-treat base.

Participants who do not experience subclinical symptoms at T1, and are thus not randomised, will not be included in the analyses.

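### Two rules remove randomised adolescents from the study for reasons close to the outcome; this conflicts with the intention-to-treat statement, and T2/T3 follow-up of those removed is not stated

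*Protocol article*

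**What the plan says.** Two sentences in the Protocol article end participation after randomisation.

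- Care as usual (CAU): "Adolescents that receive psychological care during participation in the study will not be allowed further participation".
- Randomisation and blinding, on suspected clinically significant symptoms found through monitoring: "The participant will be excluded from the study and will be transferred to more appropriate care".

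Statistical analysis then states: "Analyses are done on an intention-to-treat base". The only people it leaves out were never randomised: "Participants who do not experience subclinical symptoms at T1, and are thus not randomised, will not be included in the analyses".

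Directly after the exclusion rule, Randomisation and blinding adds: "Participants that drop out after randomisation will be asked if they are willing to complete the questionnaires at T2 and T3". This is voluntary.

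On surveillance, the Intervention section describes checks on homework and on "whether they are struggling in any way with the intervention or their mental health". It adds that "Monitoring will be done by an experienced clinical psychologist", together with a master's student. For CAU, the article describes only observation by regular medical staff, who may refer to a psychologist. The YP Face IT arm receives CAU as well.

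**The concern.** Starting psychological care and developing suspected clinical symptoms both suggest that a participant is doing badly in the domain that the trial measures. The primary outcomes are social anxiety and body esteem, and depressive symptoms are a secondary outcome. The trial enrols adolescents with subclinical symptoms, so it is foreseeable that some will cross the threshold within 25 weeks.

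An intention-to-treat analysis needs outcomes to be sought from everyone randomised. If these participants give no T2 or T3 scores, the missing values are linked to the outcome. A later analysis plan cannot recover scores that were never collected. If removal is also more frequent in one arm, the comparison is biased, and the trial's own data cannot show by how much.

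**Working it through.** **1. The passages side by side.** Statistical analysis drops no randomised participant. Care as usual and Randomisation and blinding take some randomised participants out of the study. The one sentence that could reconcile them offers T2 and T3 to those who drop out. It is not stated to cover people whom the study removes, and the wording of both removal rules points the other way.

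**2. The plan's own figure.** Inputs from Sample size: d = 0.50, r = 0.70, three linear measurements, two-sided alpha 0.025, power 0.80. With group differences of 0, 0.25 and 0.50 SD, the squared deviations from their mean sum to 0.125. The noncentrality of the group-by-time test at 56 per group is (56/2) × 0.125/(1 − 0.70) = 11.67. On 2 and 220 degrees of freedom, power is 0.799. With 50% dropout, 112/0.5 = 224. The sample size reproduces and is not in question; removals may already sit inside the 50% allowance. That allowance protects power, not against bias.

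**3. Bias from unequal removal.** The article gives no removal rates, so the rates here are assumptions. Scores are in SD units with high meaning worse. There is no true effect, and removal comes before T2, so only T1 is observed for those removed. Let a share p of an arm be removed because a state s is highest. Let s correlate ρ0 with T1 and ρ3 with T3, and let z be the normal quantile cutting off the upper p. Then:

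- m = φ(z)/(1 − p) and k = m(z + m);
- slope of T3 on T1 among those who stay: b = (r − ρ0ρ3k)/(1 − ρ0²k);
- the missing-at-random estimate of the arm's T3 mean is too favourable by B(p) = m(ρ3 − bρ0);
- bias of the comparison = B(p in YP Face IT) − B(p in CAU).

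*Example: s is the unrecorded level between visits, ρ0 = ρ3 = 0.70.*

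| p | z | m | k | b | B |
|---|---|---|---|---|---|
| 5% | 1.645 | 0.109 | 0.190 | 0.669 | 0.025 |
| 10% | 1.282 | 0.195 | 0.288 | 0.651 | 0.048 |
| 20% | 0.842 | 0.350 | 0.417 | 0.623 | 0.092 |

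Bias: 10% against 5%, 0.0477 − 0.0251 = about 0.02; 20% against 5%, 0.0924 − 0.0251 = 0.067.

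*Largest of the four trigger models: s is worsening since T1, with the state between visits correlated 0.75 with T1 and 0.80 with T3.* The SD of s is √(2 × 0.25) = 0.707, so ρ0 = −0.25/0.707 = −0.354 and ρ3 = 0.10/0.707 = 0.141. B is 0.043, 0.079 and 0.144 at 5%, 10% and 20%.

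*Upper bound: removal hits exactly the worst T3 scores, ρ0 = 0.70, ρ3 = 1.* B is 0.061, 0.116 and 0.224 at 5%, 10% and 20%.

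| Removed, YP Face IT against CAU | Level or worsening, both correlation patterns (SD) | Upper bound (SD) |
|---|---|---|
| Equal rates | 0 | 0 |
| 10% against 5% | 0.022–0.035 | 0.055 |
| 10% against 2% | 0.037–0.059 | 0.089 |
| 15% against 5% | 0.045–0.068 | 0.109 |
| 20% against 5% | 0.067–0.100 | 0.163 |

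A simulation with 1,000,000 per arm agrees to within about 0.003 SD. With these rates the bias favours YP Face IT. Swapping the rates reverses the sign.

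**4. Effect on the test.** At 56 per arm the standard error of a change-score difference is √(2 × 0.6/56) = 0.146, where 0.6 = 2(1 − 0.70). The critical value is 2.241. The false-positive rate is Φ(−2.241 + B/0.146) + Φ(−2.241 − B/0.146), with B here the bias of the comparison. It rises from 0.025 to about 0.027 at a bias of 0.022, about 0.06 at 0.100 and 0.13 at 0.163.

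**The case against.** The best defence is that nothing in the article deletes data from a randomised participant. The multilevel model keeps earlier scores, and the offer of T2 and T3 to those who drop out could be read to include removed participants. The full protocol may say so. High scorers are also screened by telephone for clinical symptoms before randomisation, which should limit early removals.

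Much of this stands. Removed participants need not vanish from the analysis, and the dropout sentence is open to the generous reading. But the article does not state that reading. Keeping T1 is also not enough when removal depends on worsening after T1 that no visit recorded.

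A reader might go further in four ways that the article does not support:

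- *That the worst outcomes are lost unequally, in favour of YP Face IT.* Closer monitoring of that arm is documented; unequal removal is inferred from it. More referrals in the CAU arm could reverse the direction.
- *That the bias is 0.11 or 0.19 SD, or 22% or 39% of the planned effect.* These are the values of m at 5% and 10%. They require removal in one arm only, of exactly the worst scores, with T1 ignored.
- *That removing referred participants changes the comparator.* The rule applies to those who receive psychological care, not to those referred, and the article places such care outside CAU.
- *That the gift card penalises unfinished sessions.* Recruitment ties it to completing the study; for those who decide to withdraw, "the adolescent will not receive a gift card". Session completion is not mentioned.

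**Conclusion.** The point holds as a conflict between the two removal rules and the intention-to-treat statement, with follow-up of removed participants left unclear. That conflict does not depend on any removal rate.

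The size is conditional. For assumed removal of 10% against 5% up to 20% against 5%, the bias is about 0.02 to 0.10 SD, with an upper bound of about 0.16 SD, against d = 0.50. It is zero if the rates are equal and there is no true effect. These figures assume normal scores, r = 0.70 between T1 and T3, removal before T2, and no T2 or T3 data from those removed. The article settles neither the true size nor the direction.

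**What to change.** Reconcile Intervention, Care as usual (CAU), Randomisation and blinding, and Statistical analysis. Leave the referral and transfer wording as it is; no view is taken here on those clinical rules. Add text to this effect:

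*Stopping the intervention, referral to a psychologist or receipt of psychological care does not end data collection. All randomised participants are invited, on a voluntary basis, to complete T2 and T3 on the same schedule and are analysed as randomised. Start of psychological care, and removals with their reasons, are recorded and reported by arm.*

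In Statistical analysis, make the analysis that sets scores to missing after the start of psychological care a sensitivity analysis only.

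The cost is a small amendment to the ethics committee during recruitment, which began in September 2019, and a few more questionnaires, online apart from the posted CBSA. Participants removed before the amendment should be reported separately by arm.
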